### Hypotheses

The principal hypothesis is as follows: Pain perceived during the collection of an arterial blood sample in the ED is lower when it is performed using positive therapeutic communication compared to neutral or nocebo communication.

The secondary hypotheses are as follows:

Discomfort perceived during the collection of an arterial blood sample in the ED is lower when the procedure is conducted using positive therapeutic communication compared to neutral or nocebo communication.Anxiety perceived during the collection of an arterial blood sample in the ED is lower when the procedure is conducted using positive therapeutic communication compared to neutral or nocebo communication.

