### Statistical Analysis

#### Sample Size Calculation

With a significance level of .05, a power of 0.9, a difference in pain on the VRS of 1.5 (generally accepted as clinically significant) with an expected SD of 2.5 [35], and an attrition of 20% on the basis of a group-independent *t* test (a specific case of linear mixed effects models [LMMs]), we must include 83 patients in each group to show the efficacy of the intervention on pain by applying the Bonferroni correction (ie, a total of 249 patients).

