#### Statistical Analysis Plan

First, descriptive statistics (frequencies and percentages for categorical data; means, SDs, medians, and IQRs for quantitative data) will be run for each measure of time for each group and the overall study sample. In addition, an analysis of nonresponses and patient dropouts will be conducted. Second, bivariate associations will be calculated to compare the groups at baseline (Pearson chi-square test, Fisher exact test, *t* test, and the Mann-Whitney test according to the distribution of variables). Third, to test the impact of the intervention on the different outcomes (hypotheses 1, 2, and 3), LMMs with patients, groups and physicians as a random effect will be performed to analyze changes over time. The participation of approximately 25 physicians is foreseen in this study. The models will be tested on all available data.

The effects of time, groups, and their interaction will be tested by controlling for sociodemographic characteristics and variables linked to health status. An intention-to-treat (ITT) analysis, per protocol (PP) and based on the analysis of communications (ie, the respect of the quality of the defined communication according to the protocol; see the next section), will be conducted. The Pearson chi-square test comparing the allocation defined in the protocol and the allocation following the analysis of communications will be performed. If necessary, a generalized LMM will also be used to explore the differences between the available measured variables (physicians having performed the ABG procedure, pain, etc). Statistical analysis will be performed on available data, and no imputation of missing data will be conducted. Given that our study will be conducted on a 1-to-1 basis with a member of the research team and on the basis of previous experience, we expect that the number of missing values will be low. Statistical analyses will be performed using the R (R Core Team and the R Foundation for Statistical Computing) and STATA version 12 (StataCorp); the level of significance will be set at *P*=.05.

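### The trial is sized with a Bonferroni correction, but the analysis section sets P=.05 without carrying that correction to the two primary pain contrasts

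*Protocol article*

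**What the plan says.** Three places in the protocol article bear on this.

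- **Hypotheses.** The principal hypothesis is that pain "is lower when it is performed using positive therapeutic communication compared to neutral or nocebo communication". That gives two contrasts, positive versus neutral and positive versus nocebo, joined by *or*. The section does not say that both must succeed.
- **Sample Size Calculation.** The inputs begin "With a significance level of .05, a power of 0.9, a difference in pain on the VRS of 1.5", "with an expected SD of 2.5", with 20% attrition, "on the basis of a group-independent *t* test". The result, 83 per group, is said to be enough "to show the efficacy of the intervention on pain by applying the Bonferroni correction (ie, a total of 249 patients"). The number of comparisons corrected for and the sidedness are not given.
- **Statistical Analysis Plan.** Tests of time, group and their interaction in linear mixed models are planned for hypotheses 1 to 3. Intention-to-treat, per-protocol and communication-based analyses are listed. The section ends by saying that "the level of significance will be set at" P=.05. No correction is mentioned, no pairwise contrast is named, and the level is not described as overall or per comparison.

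**The concern.** The level at which the primary comparisons are judged should be the level for which the trial was sized. Here the sizing uses a corrected level, while the only decision level in the analysis section is an uncorrected-looking .05. Because the principal hypothesis joins its two contrasts by *or*, a reader could declare success if either falls below .05. The trial would then have two opportunities to reject at the full level, and the 5% error rate would not be held.

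The practical risk lies in the gap between the two levels. Suppose one pain contrast gives p = .035 and the other is clearly non-significant. Judged at .05 per contrast, the hypothesis is supported. Judged at .025 per contrast, it is not. The text does not settle which applies, so the choice could be made after the data are seen.

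**Working it through.** **1. Was the sample size really computed with a corrected level?**

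Inputs from Sample Size Calculation: difference 1.5, SD 2.5, power 0.90, attrition 20%, overall level .05. Assumptions: two-sided testing and a correction for two contrasts (.05/2 = .025 each), since neither is stated.

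n per group = 2 (z₁₋α/₂ + z₀.₉₀)² × (SD/difference)²

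- At α = .025: 2 × (2.241 + 1.282)² × (2.5/1.5)² = 2 × 12.41 × 2.778 ≈ 68.95, so 69. Then 69 × 1.2 = 82.8, so **83**. This matches the stated figure.
- At α = .05, uncorrected: 2 × (1.960 + 1.282)² × 2.778 ≈ 58.4, so 59 (60 with the t distribution). After attrition this gives 71 to 75, depending on how attrition is applied. It does not give 83.
- One other route also reaches 83: a one-sided t test at .05/3 gives 66, and 66/0.8 = 82.5, so 83. That is a corrected level too.

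Every route tried that reaches 83 uses a corrected level. The correction was applied in the sizing and not merely mentioned.

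**2. What error rate follows if each pain contrast is tested at .05?**

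With equal arms, the two contrasts share the positive arm. Their test statistics therefore have correlation (σ²/n) / (2σ²/n) = 0.5. With no true differences and c = 1.96:

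Family-wise error = 1 − P(|Z₁| < c and |Z₂| < c), for a bivariate normal with correlation 0.5.

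| Level per contrast | Either contrast rejected, either direction | Either contrast rejected in favour of positive communication |
|---|---|---|
| .05 | 9.1% | 4.5% |
| .025 (Bonferroni) | 4.6% | 2.3% |

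A simulation of 4 million trials gives 9.05% for the first cell. If the two tests were independent, it would be 1 − 0.95² = 9.75%. For a single two-sided test at .05, the comparable figures are 5% and 2.5%.

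**3. What does a corrected rule cost in power?**

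With 69 evaluable per group, power per contrast at two-sided .025 is 90.0% by the normal formula and 89.4% by the t test. That is the power for which the trial was planned. Holm's procedure rejects whenever Bonferroni does, so it cannot have less power.

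One caveat is unrelated to the choice of level. Adding 20% to 69 does not fully offset a 20% loss: 83 × 0.8 = 66.4, and with 66 evaluable the power at .025 is 88.6% (normal) or 87.9% (t test).

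**The case against.** The strongest reply is that nothing has been dropped. The sample-size text starts from the same .05 and applies Bonferroni to it, so .05 is the overall level there. The analysis text, under the same Statistical Analysis heading, may simply repeat that overall level. On that reading sizing and analysis agree. This stands as far as it goes: a reader might infer that the plan abandons the correction, but the document never says so, and the 9% is conditional on the per-test reading.

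Second, the analysis section names group, time and interaction effects and no pairwise contrasts. If a single two-degree-of-freedom group test at .05 had to succeed first, the error for the two contrasts would be about 4.2% when no arm differs. But no such gate is written. An omnibus test alone would not answer the principal hypothesis either, because a difference between nocebo and neutral could drive it.

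Third, 9% is not the rate of false wins. It counts rejections in both directions, whereas the hypothesis is directional. The rate of false claims for positive communication is about 4.5%, against 2.5% for one two-sided test. That is accepted.

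Two larger readings are not supported. Testing all three pairs at .05 would give about 12.2%, but neutral versus nocebo is not part of the principal hypothesis. A reader might also take the three listed analyses as further chances to win. Nothing says that a per-protocol or communication-based result can establish the hypothesis, and the abstract mentions only the intention-to-treat analysis.

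Finally, contrast coding and testing order can fairly be left to a fuller plan. But the article does fix an analysis level, and as written that level does not carry the correction on which its own sample size rests. This is more than an omitted detail.

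**Conclusion.** The point holds as a mismatch that leaves the primary decision rule open. It does not hold as proof that the correction was withdrawn. The sample size reproduces at a corrected level, while the analysis section states P=.05 and does not apply the correction to the two pain contrasts.

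Taken literally as a per-test level, this gives a two-sided family-wise error of about 9% instead of 5%, and about 4.5% instead of 2.5% for false wins for positive communication. These figures assume equal arms, approximately normal test statistics, no true differences between arms, and success declared on either contrast. If .05 is meant as the overall level, there is no inflation, but the text needs to say so. Because this concerns the primary outcome, it should be settled before the data are analysed.

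**What to change.** Add a sentence to the Statistical Analysis Plan section along these lines: *The confirmatory family consists of the two intention-to-treat contrasts on pain, positive versus neutral and positive versus nocebo, estimated from the mixed model. The overall two-sided level is .05, controlled by Holm's procedure: the smaller p-value is compared with .025 and, if that contrast is significant, the other is compared with .05. Per-protocol, communication-based and secondary-outcome tests are supportive and are reported at nominal .05.*

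Testing each contrast at .025, as in the sample size, is an acceptable alternative. With no true differences, either rule gives a family-wise error of about 4.6%, since Holm's first step is the Bonferroni test. It would also help to state in Sample Size Calculation that the correction is for two two-sided contrasts, if that is what was meant.

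The cost is a few lines of text. The total of 249 does not change, and no power is lost against the plan, because the sizing already used a corrected level.

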#### Analyses of Communications

All communications will be recorded. We will listen to 30 communications at a time to evaluate the quality of each communication and to ensure that the communication corresponds to the defined study arm defined at the time of randomization. This evaluation will be performed until less than 10% of incorrect rankings are obtained. A physician external to patient management will reassign the patient groups based on a list of preselected keywords. This same physician will then (re)classify the patients into 1 of the following 3 arms: therapeutic positive communication, nocebo, or neutral.

The classification will be performed with the help of a list of 10 keywords provided to the external physician. Each list of 10 keywords will be associated with 1 of the 3 arms and will correspond to standardized phrases related to each arm. Thus, if the external physician finds 1 keyword associated with the nocebo arm, the patient will then be reclassified into the nocebo arm; if the external physician finds 1 keyword associated with the therapeutic positive communication arm but without any keywords associated with the nocebo arm, the patient will be classified into the therapeutic positive communication arm. If the physician does not find any keywords associated with these 2 arms, the patient will be classified into the neutral arm.

This classification will be conducted in parallel by 2 persons for the first 30 patients to evaluate the interrater reliability using Cohen κ. If κ>0.90, only 1 coder will continue to code the audio recordings. If not, 2 coders will continue to evaluate the communications; in the case of disagreement, a third coder will make the final decision.

The keywords associated with the nocebo group are as follows:

PainColdPrickDo not panic.Are you in pain? I am going to prick.This is going to sting.Do not move, it won’t be long.Do not be frightened.How do you feel?

The keywords associated with the therapeutic positive communication group are as follows:

Be reassured.Are you comfortable?Are you relieved?I am going to place the drip.Have confidence.Take it easy.It will be fast.Do you feel well?

These lists are likely to be adapted based on the audio recordings.

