### Intervention Groups

During each step of the sampling (identification, disinfection, sampling) for the ABG procedure, the physician involved will communicate with the patient with a preestablished speech according to the assigned study arm. Communication sentences for each intervention group are presented in Table 1. In the case of failure of the first puncture, the intervening doctor will be able to use the second set of sentences corresponding to the assigned intervention group (also in Table 1).

**Table 1 table1:** Study arms.

Study arm	Intervention/treatment
Positive therapeutic communication: Solicit the subconscious mind of the patient by asking questions that are not focused on the ABG^a^ procedure. This process allows to divert the attention of the brain to more pleasant information and thus modulate the painful information. This is a standardized intervention with precise phrases.	The positive therapeutic communication group physician will say: During identification of the arterial blood collection site: “Are you comfortably installed?,” “How old did you say you were?,” etc At the time of disinfection: “How did you get to the hospital?,” “What day is it?,” etc At the time of puncture: “What is the noise of the lights at your home?,” “Does your car still go to the shops?,” etc
Nocebo: Use of words with a negative connotation (words used frequently in daily practice in the ED^b^)	The nocebo group physician will say: During identification of the puncture site: “That’s where I am going to prick you,” “I am looking for the place where I will prick,” etc At the time of disinfection: “Watch out, it is cold,” “It is disagreeable,” “I am disinfecting the site,” etc At the time of puncture: “Watch out! I am going to prick…1, 2, 3…I am pricking,” “Watch out, this is going to hurt, I am pricking,” etc
Neutral: Use of words defined as neutral (ie, no negative or positive connotation but based on the description of precise facts)	The neutral group physician will say: During identification of the site: “I am taking your pulse,” “I am identifying the artery,” etc At the time of disinfection: “I am disinfecting the site,” “I am cleaning your skin,” etc At the time of puncture: “I am taking the sample,” “I am performing the puncture,” etc

^a^ABG: arterial blood gas.

^b^ED: emergency department.

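### The keyword rule makes neutral the leftover class, so an unspoken neutral script scores as correct delivery and keyword-free procedures from the other arms join the neutral group

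*Protocol article*

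**What the plan says.** The Analyses of Communications section describes keyword lists as follows: "Each list of 10 keywords will be associated with 1 of the 3 arms and will correspond to standardized phrases related to each arm". It then gives the rule in three steps.

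- Nocebo: "if the external physician finds 1 keyword associated with the nocebo arm, the patient will then be reclassified into the nocebo arm".
- Positive: the coder "finds 1 keyword associated with the therapeutic positive communication arm but without any keywords associated with the nocebo arm".
- Neutral: "If the physician does not find any keywords associated with these 2 arms, the patient will be classified into the neutral arm".

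These three arms are the only classes. The article prints a nocebo list and a positive list and says that the lists may be adapted in the light of the recordings. Recordings are heard in batches of 30, and "This evaluation will be performed until less than 10% of incorrect rankings are obtained".

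Table 1, under Intervention Groups, defines the neutral arm as "Use of words defined as neutral (ie, no negative or positive connotation but based on the description of precise facts" and gives example sentences for site identification, disinfection and puncture. The Neutral Arm section adds that these terms serve to describe the procedure and tell the patient how it is proceeding.

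The Statistical Analysis Plan section uses the classification in two ways: a Pearson chi-square test of allocated against classified arm, and an outcome analysis based on the communication delivered, named alongside intention-to-treat and per-protocol analyses.

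**The concern.** Two of the three classes need evidence that something was said. The third is assigned when nothing relevant was found. The announcement of a list for each of three arms implies a neutral list, but no step of the rule consults one. The neutral arm is defined as an active factual commentary, so silence or unrelated talk is not the neutral intervention. The rule cannot tell the two apart.

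Non-delivery is a risk that the article itself raises. Strengths and Limitations notes that inexperienced physicians may concentrate on technique at the expense of the communication, and it relies on replaying the recordings to check that what was received matches what was allocated. For non-delivery in the neutral arm, the keyword step offers no such check.

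Two things are at stake. The fidelity tally is asymmetric: the same lapse is an error in the positive and nocebo arms and a success in the neutral arm. The communication-based neutral group, a comparator in the principal hypothesis, becomes a mixture of procedures with the neutral script, with no script, and with positive or nocebo speech that the keywords did not capture.

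**Working it through.** The plan states no figure on this point that could be reproduced. The check is the rule itself, followed by illustrations under stated assumptions.

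**Step 1: the rule as a truth table.** Its inputs are whether a nocebo keyword was found and whether a positive keyword was found.

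| Nocebo keyword | Positive keyword | Class |
|---|---|---|
| no | no | neutral |
| no | yes | positive |
| yes | no | nocebo |
| yes | yes | nocebo |

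Neutral speech is not an input. A usable recording with no keyword always falls in the first row: correct if the patient was allocated to neutral, an error otherwise.

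**Step 2: can keyword-free recordings arise in the other arms?** I compared the Table 1 example sentences with the printed lists by exact wording. None of the 6 positive examples contains a printed positive keyword (the one about being comfortably installed is a near match), and 2 of the 7 nocebo examples contain no nocebo keyword. The examples are incomplete, the lists may be adapted, and the trial is conducted in French, so this gives no rate. It shows only that the first row can be reached from any arm. The default would remain a problem even with perfect positive and nocebo lists.

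**Step 3: make-up of the communication-based neutral group.** Assume that a share f of procedures in every arm contains no keyword of any arm, including neutral, and that all others are classified as allocated. The documents give no value for f. With 83 per arm (Sample Size Calculation):

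- Size of the classified neutral group: 83 + 2 × 83 × f.
- Those without a captured neutral script: 3 × 83 × f.
- Those who come from the other two arms: 2 × 83 × f.

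| f | No captured neutral script | From the other arms |
|---|---|---|
| 5% | 12.45 / 91.3 = 13.6% | 8.3 / 91.3 = 9.1% |
| 10% | 24.9 / 99.6 = 25.0% | 16.6 / 99.6 = 16.7% |
| 20% | 49.8 / 116.2 = 42.9% | 33.2 / 116.2 = 28.6% |

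The 83 cancels, leaving 3f / (1 + 2f) and 2f / (1 + 2f). The result needs equal arms, not that particular size.

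**Step 4: the batch criterion.** Fewer than 10% errors in 30 means at most 2. Assume 10 patients per arm in a batch.

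- If only neutral scripts go unspoken, the chance of 3 or more errors is 0 at every rate under the written rule. If a neutral keyword were required, it would be P(Bin(10, q) ≥ 3) = 0.07, 0.62, 0.945 and 1.00 for q = 10%, 30%, 50% and 100%.
- If a share q is keyword-free in every arm, the chance of passing is P(Bin(20, q) ≤ 2) under the written rule, against P(Bin(30, q) ≤ 2) if all arms could be checked: 0.677 against 0.411 at q = 10%, 0.405 against 0.151 at 15%, and 0.206 against 0.044 at 20%.

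These figures apply to silence or wholly keyword-free talk only.

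**The case against.** The strongest reply is that the rule was meant to detect contamination. Table 1 defines neutral partly by the absence of positive or negative connotation, and Strengths and Limitations gives avoiding contamination of the arms as one purpose of the replay. Absence of loaded words serves that purpose. This stands in part: neutral fidelity can fail, because one nocebo or positive keyword is enough. But both descriptions of the arm also require factual description, which the rule never looks for.

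Other checks exist. Batches are heard for quality, an independent monitor compares communication with allocation for the first 30 patients, and the case report form records the type of words used according to the patient. A listener might well notice silence. None of these states a criterion for neutral delivery, and none changes the class that the rule assigns.

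The assumed rates can also be challenged, and rightly. Off-script talk would often trigger the nocebo list, which contains single common words, so keyword-free talk may be rarer than off-script talk in general.

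Two stronger readings are tempting. One is that a blank or failed recording counts as correct neutral delivery. The article does not say so: analyses use available data without imputation, so a failed recording may simply be missing. Even if blanks were coded, they would be errors in the other two arms. The other is that the per-protocol arms are filtered by different standards. The text does not say that this classification defines the per-protocol set.

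Finally, the neutral list may appear in the full protocol, and its absence from the article is not the point. The rule is stated in full and has no step that would use such a list.

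**Conclusion.** The concern holds for usable recordings without keywords. As written, the rule scores an undelivered neutral script as correct and transfers keyword-free positive and nocebo procedures to the neutral group. It is at odds with the one-list-per-arm statement and with the definition of neutral as spoken description. The under-10% criterion, the chi-square test and the communication-based analysis are affected. The per-protocol analysis is affected only if its set is built from this classification.

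The size is unknown because the rate of keyword-free procedures is unknown. The 14% to 43% range is an illustration that rests on f = 5% to 20%, equal in all arms, with no other misclassification. The batch probabilities also assume 10 patients per arm in each batch.

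A reader might infer that the main trial result is compromised, or that neutral-arm fidelity can never fail. Neither follows: intention-to-treat uses the allocated arm, and contamination in the neutral arm is still detected. The point deserves correction because the delivered-communication results would otherwise be misread, but it does not threaten the randomised comparison.

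**What to change.** In Analyses of Communications:

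1. Classify as neutral only if at least one keyword specific to the neutral arm is present and no nocebo or positive keyword is present. Leave out phrases shared between arms. The sentence announcing disinfection of the site stands in both the nocebo and neutral rows of Table 1, so it cannot identify either arm.
2. Add a fourth code, script not delivered or not classifiable, for usable recordings with no arm-specific keyword. Count it as incorrect delivery in all three arms, show it in the table of allocated against classified arm, and leave it out of the communication-based groups.
3. Report missing or inaudible recordings separately by arm as missing, not as neutral. Note this status before the audio is erased after transcript verification.
4. State whether the per-protocol set uses this classification.

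The cost is one changed sentence and one extra code, with the same coder and recordings. The communication-based groups become slightly smaller, and reported neutral-arm fidelity may fall. One limit remains: a single keyword would still pass a script spoken at only one of the three steps, as it already does in the other arms. The intention-to-treat analysis does not change.

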#### Data Monitoring

No data related to the research foreseen will be obtained via laboratory tests or invasive procedures. The sources of materials are as follows:

Data of quantitative interviews, heteroadministered by the evaluator using a paper CRF. The data will then be entered into REDCap.Patient screening data collected by the senior TD.Data of audio recordings collected during the ABG procedure with the use of an audio recorder. Recordings will be transcribed for analysis in Microsoft Word.Patient information letters as well as the consent forms to be completed will be stored in a dedicated secure box for the study in the ED.

As this is a low-risk study, the following monitoring activities will be carried out by a person independent of the study and trained in good clinical practices and the protocol:

A qualification visit will be conducted prior to the start of the study.The initiation visit will be conducted in the HFR ED in the presence of the PI and the research team.A follow-up visit after the inclusion of the first 3 participants will be carried out and if necessary repeated in the case of major problems encountered.Regular monitoring (minimum once every 3 months) will be carried out to (1) check that all patients have provided oral consent before inclusion and written consent after the procedure, (2) check that documents are stored according to the protocol (consents, paper CRFs, etc), (3) verify paper CRF data extracted from the patient records (at least 20% of data randomly selected), (4) verify the concordance of the information in REDCap and the information in the paper CRFs (at least 20% of the randomly selected data), and (5) verify the adequacy of the caregivers' communication with the allocation arm for the first 30 patients included. Control visits will be conducted if the actual communication differs from the allocation arm in more than 10% of cases.

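### The printed positive keywords do not match the positive script in Table 1, so positive communication delivered as scripted can be coded neutral in the communication-based analysis

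*Protocol article*

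**What the plan says.** The section Analyses of Communications has an external physician reassign each patient to an arm from the recording, using keyword lists. The lists are described so: "Each list of 10 keywords will be associated with 1 of the 3 arms and will correspond to standardized phrases related to each arm". The rule works in order:

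- One nocebo keyword makes the recording nocebo, whatever else is said.
- A recording is positive "if the external physician finds 1 keyword associated with the therapeutic positive communication arm but without any keywords associated with the nocebo arm".
- Otherwise: "If the physician does not find any keywords associated with these 2 arms, the patient will be classified into the neutral arm".

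The printed positive list has eight entries and opens "Be reassured.Are you comfortable?Are you relieved?I am going to place the drip". The other four are short reassurances about confidence, calm, speed and well-being. The section closes by saying that the lists will probably be adapted in the light of the recordings.

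Table 1 (Intervention Groups) prints two positive phrases per step, and each step ends in an open etc. At identification they ask whether the patient is comfortably settled, and the patient's age. At disinfection they ask about the journey to hospital, and the day. At puncture they ask about the noise of the lights at home, and "Does your car still go to the shops". The section Positive Therapeutic Communication Arm describes the last sentence as the confusion question that diverts attention.

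The coded arm is used in the communication-based analysis, in a chi-square comparison of allocated and coded arm (both in Statistical Analysis Plan), and in a rule that coding checks continue in batches of 30 until fewer than 10% are misclassified.

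**The concern.** A list meant to recognise the positive script consists mostly of reassurances, while the printed script consists mostly of distraction questions. Since neutral is the residual class, a positive recording that the list does not recognise is not left unclassified. It is counted as neutral, the arm it should be compared with. The error runs one way and pulls the positive-versus-neutral contrast toward zero. It also makes faithful delivery look like poor fidelity. The Strengths and Limitations section relies on replaying the recordings as its safeguard against contamination of the arms.

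A second weakness lies in the same rule. It does not say that only the physician's words count, or only words spoken before the needle goes in. The recording runs until collection is finished, and the nocebo list includes an enquiry about pain and phrases telling the patient not to panic or be frightened. A physician may say these in reaction to a patient who is hurting, so the outcome could influence the coded arm.

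**Working it through.** **1. List against script.** I compared the eight printed keywords with the six printed positive phrases.

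| Step | Printed positive phrase (paraphrased) | Keyword present? |
|---|---|---|
| Identification | comfortably settled | not verbatim; near match to the comfort keyword |
| Identification | age | no |
| Disinfection | journey to hospital | no |
| Disinfection | day | no |
| Puncture | noise of the lights | no |
| Puncture | car and shops | no |

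Verbatim matches: 0 of 6. With lenient matching: 1 of 6. Conversely, "I am going to place the drip" belongs to no step of an arterial puncture.

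**2. The rule applied to on-script recordings.** Taking one printed phrase per step gives 2 × 2 × 2 = 8 positive, 2 × 3 × 2 = 12 nocebo and 2 × 2 × 2 = 8 neutral combinations.

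- Verbatim matching: 8 of 8 positive combinations are coded neutral.
- Lenient matching: 4 of 8 are coded neutral, namely those that open with the age question.
- Under both, nocebo (12 of 12) and neutral (8 of 8) are coded correctly.
- If all six positive phrases are spoken, the recording is coded neutral under verbatim and positive under lenient matching.

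If the six Table 1 phrases were themselves the keywords, 8 of 8 positive combinations would be coded positive and the other arms would stay correct.

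**3. The plan's own sample size, used only for scale.** Inputs from Sample Size Calculation: difference 1.5, SD 2.5, power 0.9, alpha 0.05 with Bonferroni, attrition 20%. Two comparisons and two-sided testing are my assumption:

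n = 2 × (2.241 + 1.282)² × 2.5² / 1.5² = 68.95, so 69; 69 × 1.2 = 82.8, so 83 per group. This matches the plan.

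**4. Dilution.** Let m be the share of correctly treated positive patients coded neutral, unrelated to their pain. The neutral class then holds 83(1 + m) patients, of whom 83m received positive communication. Apparent difference = 1.5 − 1.5 × m/(1 + m) = 1.5/(1 + m).

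Power uses a normal approximation at two-sided alpha 0.025, with 80% of each class analysed. The neutral-class variance is 2.5² + f(1 − f) × 1.5², where f = m/(1 + m).

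| m | Positive class | Apparent difference | Power |
|---|---|---|---|
| 0 | 83 | 1.50 | 0.89 |
| 25% | 62.25 | 1.20 | 0.66 |
| 50% | 41.5 | 1.00 | 0.40 |
| 100% | 0 | none estimable | – |

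**5. The 10% coding rule.** With equal arms, perfect delivery and no other coding error, the overall misclassification rate is m/3. It reaches 10% at m = 30%. At m = 50% it is 16.7%, and the binomial chance of 3 or more wrong in a batch of 30, which fails the rule, is 0.90.

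**The case against.** The strongest reply is that the lists are declared provisional and the printed script is incomplete. Every step in Table 1 ends in etc, a second set of sentences is mentioned but not shown, and only eight of the stated ten positive keywords are printed. The section on the positive arm says its first two sentences carry reassuring words, which is what the list contains. A physician, not a string matcher, does the coding. The trial is apparently run in French, so verbatim matching of English renderings is only indicative. Nor does Table 1 say that one phrase is chosen per step: if both identification phrases are spoken and matching is lenient, nobody is miscoded. Finally, comparing coded with allocated arm might expose the fault in the first 30 recordings.

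Much of this stands, and it is why m must be shown as a range that starts at 0. It does not remove the mismatch. Translation or lenient reading rescues the comfort phrase only; the other five printed phrases differ from the keywords in meaning. Adapting the lists without a lock point or blinding to outcomes leaves the classification unfixed. Two coders can agree perfectly while applying the same unsuitable list, so a high kappa gives no reassurance.

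Three stronger readings are tempting but not supported:

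- *The per-protocol analysis is corrupted.* The Statistical Analysis Plan sentence leaves unclear whether per protocol is defined by this coding, so any effect on it depends on that reading.
- *The monitoring trigger would fire falsely.* Data Monitoring says "Control visits will be conducted if the actual communication differs from the allocation arm in more than 10% of cases", but does not say that the monitor uses the keyword lists.
- *Patients in most pain will be moved into nocebo.* The Introduction presents some of these phrases as ordinary negative wording by caregivers, and Data Confidentiality describes the recordings as physician communication. Reverse causation is a plausible risk that the rule leaves open. It is not a shown effect and has no size here.

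**Conclusion.** The concern holds for the communication-based analysis, the chi-square comparison of allocated with coded arm, and the 10% misclassification rule in Analyses of Communications. The printed positive list contradicts the plan's statement that it "will correspond to standardized phrases related to each arm", and the neutral default sends unrecognised positive recordings to the comparator. Intention-to-treat by randomised arm is untouched.

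The mismatch itself is read directly from the document. Its size is conditional: the apparent difference ranges from 1.5 points (m = 0) to 1.0 (m = 50%), with no positive class left at m = 100%. These figures assume a true difference of 1.5 and miscoding unrelated to pain. The power figures also assume SD 2.5, 20% attrition and two-sided alpha 0.025. The document does not allow m to be estimated.

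**What to change.** - Rebuild the positive keyword list from the full scripted phrases, including the puncture-time questions, and remove the drip phrase.
- State that only the physician's words count, up to the first needle insertion, with the scripted puncture sentence falling inside that window.
- Adapt the lists once, after the first 30 recordings, by people without access to outcomes. Then lock them, and recode earlier recordings from the transcripts.
- Label the communication-based analysis as supportive to intention-to-treat, and say whether the per-protocol set uses this coding.

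A separate neutral list is not needed for the rule to work.

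The cost is one rewritten list, a few sentences and a small amount of recoding, with no patient contact. Since audio files are to be erased once transcripts are verified, the transcripts should mark the speaker and the moment of puncture before that happens.
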